### Follow-up

Recruitment strategies for the study include adapted routine ASA procedures that are recorded on the appropriate forms. Initially, identification, demographic, and socioeconomic variables are recorded along with type and length of time of index case cohabitation. The contacts are duly informed concerning the clinical forms of the disease, incubation periods, signs and symptoms, modes of transmission, and treatment regimens.

The contacts are submitted to a detailed physical examination including verification of a BCG scar, sensitivity testing, and a traditional dermatological examination to identify suspected leprosy lesions. The neurological evaluation covers inspection and palpation/percussion, together with the functional evaluation of the peripheral nerves and identification of deformities [18]. The cases detected in the initial evaluation are considered coprevalent contacts of their index cases, thus becoming index cases themselves and triggering a contact search.

After this first stage, signed informed consent is obtained from all participants aged 18 and over in addition to the parents/guardians of those up to 17 years of age. A signed assent form is also required for the 12- to 17-year-old participants.

The informed consent form includes: a medical description of leprosy; the role played by contact surveillance in disease control; the study objectives; the risks and benefits related to intervention; the commitment to participate in the study, including an initial evaluation, another after 2 months, and a third upon completing 1 year; concealed randomization of group participation; the possibility of the occurrence of adverse events; and the procedures to be followed if further assistance is needed accompanied by the data necessary to contact team members.

After signing the forms, 16 ml of blood is collected from adults and contacts aged 12 to 17 years for the baseline identification of the following immunological markers: anti-PGL-1, anti-LID-1, and IFN-γ during the first evaluation, at the end of the second month (prior to BCG immunization), and 12 months subsequent to the initial intervention. All participants will undergo digital pulp blood sampling for rapid anti-PGL-1 testing during the initial evaluation and after 12 months following intervention. Children under 12 years of age will have only a digital pulp blood sample collected for rapid anti-PGL-1 test. This test has been validated by Bührer-Sékula et al. [10], and a simple verification of the agreement with the results of the enzyme-linked immunosorbent assay (ELISA) (anti-PGL-I) in adults will be conducted in this study to inform of the limitations of the results in children, for whom ELISA (anti-PGL-I) will not be available.

Lymph from the right earlobe is obtained by dermal scraping for DNA/ML molecular investigation (PCR) during the first evaluation, but only from the participants over 12 years of age, since children under 12 years of age are less able to bear the discomfort. Another lymph sample is collected at the end of the second month in the event the result of the first examination is either positive or inconclusive. Lymph collection follows MH guidelines, according to which the specimen is stored in a sterile bottle immersed in a 70% alcohol solution [19].

The BCG vaccine is administered 2 months after the first clinical assessment has been made in contrast to the MH recommendation in that regard [18]. This alteration makes it possible to evaluate the immunological parameters of each participant in response to rifampicin alone on the one hand, and the placebo alone on the other. Since rifampicin has a significant bactericidal effect, a 2-month interval between the administration of rifampicin and BCG is planned to avert interference of the antibiotic in the immune response to this attenuated live vaccine. Because of the slow progression of leprosy disease, however, the postponement of BCG vaccination for up to 2 months after receiving rifampicin should not substantially interfere with the protection conferred by BCG. Contacts under 1 year of age will be administered BCG only if they have not been vaccinated before. We clarified that participants are encouraged to seek care at the ASA Outpatient Clinic any time they present signs or symptoms indicated in the baseline interview. The flowchart of the trial is show in Fig. 1.

**Fig. 1 Fig1:**
[figure not shown]
Flowchart of the clinical trial of chemoprophylaxis with rifampicin in contacts of multibacillary leprosy patients. BCG-ID, Bacillus Calmette-Guérin intradermally; ICF, informed consent form; MDT, multidrug therapy

The study is expected to last a total of 6 years with the understanding that all contacts participate in a minimum 1-year follow-up period. To minimize losses during that time, a search will be carried out in the official MH leprosy database, or SINAN, to identify new leprosy cases among ASA contacts that were originally diagnosed in another health care unit. The search variables will include the full names of the contact and his/her mother in addition to the date of birth of the former. Those who were not treated at ASA and are not on the SINAN database will be considered healthy.

The schedule of enrollment, interventions, and assessments of the study is shown in Fig. 2, Additional file 1. The “Close-out” is the end of follow-up for the study since participants will continue to have access to the outpatient clinic on a routine basis, as will all contacts. All participants are assessed at fixed points: upon recruitment/allocation, and after 2 and 12 months. Afterwards, case ascertainment continues until July 2021 as participants are encouraged to return whenever signs/symptoms (to which they are alerted) appear, or SINAN database discloses a new case that belongs to the study cohort.

**Fig. 2 Fig2:**
[figure not shown]
Schedule, enrolment, intervention and assessments for the clinical trial of chemoprophylaxis with rifampicin in contacts of multibacillary leprosy patients. IFN, interferon; LID, leprosy Infection Disease Research Institute diagnostic; PCR, polymerase chain reaction; PGL, glycolipid phenolic

### Adverse events

Adverse events and clinical complications will be monitored throughout the study period. The symptoms and signs temporally related to the intervention are recorded on a specific form, regardless of any presumed causal association with the intervention.

While the probability of the occurrence of adverse events related to the administration of a single dose of rifampicin is low, the most common ones have been loss of appetite, nausea, vomiting, diarrhea, and orange or reddish coloration of urine, saliva, feces, sweat, and tears. There may also be occurrences of colitis, facial flushing, hives, rashes, jaundice, liver failure, red spots on the skin, bleeding from the nose, gums, or vagina, anemia, flu symptoms, fever, weakness, headache, tremors, mental confusion, motor coordination disorders, transient visual changes, peripheral neuritis, and venous thrombosis [15].

Following blood collection, pain and bruising may take place at the puncture site, and auricular lobe lymph collection may also cause transient pain at the collection site.

In accordance with MH guidelines, BCG vaccination may lead to adverse reactions at the application site and in satellite lymph nodes, while severe systemic reactions [18] have very rarely been known to occur.

### Laboratory methods

#### Serology for anti-PGL-1 and anti-LID-1

Serology is performed prior to administration of rifampicin/placebo, and 2 and 12 months after chemoprophylaxis. As such, 96-well plates are coated with 1 μg/ml recombinant LID-1 or PGL-1 protein in a bicarbonate buffer for 18 h at 40 °C and blocked for 1 h at room temperature with phosphate-buffered saline (PBS)-Tween containing 1% bovine serum albumin (BSA). Serum samples are diluted in 0.1% BSA, added to each well, and incubated at room temperature for 2 h accompanied by shaking. Plates are washed and IgM HRP (Rockland Immunochemicals, Gilbertsville, PA, USA), is diluted in 0.1% BSA and then added to each well before incubation at room temperature for 1 h with shaking. After washing, the plates are developed with the peroxidase substrate, and the reaction is terminated by adding 1NH_2_SO_4_.

#### ML flow test

A digital pulp blood sample will be submitted to the rapid test ML Flow implemented as part of the contact’s routine examination in the ASA Outpatient Clinic in 2003. The test is read after 5 and 10 min and the result is considered valid when the control line is visible, and considered positive when a distinct staining reddish line is observed. When no staining or only a faint staining is visible the result is considered negative, as described by Bührer-Sékula and coworkers [10].

#### Whole blood test for evaluation of the cellular immune response

Heparinized whole blood is diluted 10 times in serum-free culture medium (RPMI 1640 supplemented with 100 U/ml penicillin, 10 μg/ml streptomycin, and 2 mM l-glutamine). The culture is stimulated or not with 10 μg/ml irradiated *M. leprae*. After 5 days, the plasma is collected to assess the concentration of IFN-γ using ELISA.

#### PCR for DNA detection of *M. leprae*

The biological samples are collected according to MH and World Health Organization (WHO) recommendations and stored in a freezer at −70 °C or liquid nitrogen until processed. Samples of contact dermal scrapings of the right earlobes are likewise collected as per MH recommendations regarding leprosy diagnosis [16].

DNA extraction from the dermal scrape samples is performed using the DNeasy Blood and Tissue Kit as per the manufacturer’s instructions (QIAGEN®) and aided by an extractor robot.

Real-time PCR assay is standardized to amplify a 16S gene sequence to determine the relative number of bacteria in the contact biological samples [13]. PCR reactions are prepared with Applied Biosystems reagents (Mastermix®) to a final volume of 25 μl.

### Statistical analysis

The evaluation of the efficacy of chemoprophylaxis will be based on the occurrence of new cases of leprosy in both groups and will be measured at least at 1 year after the single dose of rifampicin. Over the period of 1 year, three evaluations will be carried out: at baseline, 2 months, and 12 months.

The total number of randomized participants will be analyzed to preserve the safeguards against selection bias and confounding (“intention-to-treat analysis”). An alternative analytical strategy (“per-protocol analysis”) will disregard the data obtained from participants that did not meet the eligibility criteria and did not adhere to either of the intervention regimens or study procedures.

Evaluating the group that adhered to the protocol prevents classification bias that may result from analyzing the participants in the originally allocated group despite their not having followed the specifically planned procedures**.** Any discrepancies in the results of the two analytical strategies will be interpreted in light of the distribution of the baseline characteristics of the participants adhering to the protocol. The balanced distribution of covariates across comparison groups achieved by randomization could be lost as a result of violations in protocol.

The main explanatory variable defined by the study design is the intervention (rifampicin/placebo). Whereas univariate analyses will be performed to describe their baseline characteristics, bivariate analyses will explore the association between intervention and outcomes (response variables). Multivariate analyses (Cox regression) will be conducted to adjust the association estimates (hazard ratio for new cases) for covariates with any imbalance in group distribution. Subgroup analyses of effectiveness (derivatives of the measures of association) according to age, along with the BI and type of cohabitation with the index case, will be carried out.

Cox regression is used to estimate the conditional hazard ratio and the survival function based on longitudinal data from a dynamic cohort of individuals under surveillance for different periods. The hazard ratio estimates the magnitude of the association between chemoprophylaxis and leprosy. The measurement takes into account the different time periods that have elapsed between exposure (treatment/placebo) and the outcome (illness) for each participant until disease develops or follow-up is discontinued [20]. The survival curve will be required to handle open and continuous recruitment as well as censorship, and the survival rates can be estimated by conditional probability according to the strategy proposed by Kaplan and Meier. The statistical significance will be assessed by the Log-Rank test [21].

For all the analyses, a 5% significance level will be adopted, and 95% confidence intervals constructed for the estimates.

An interim analysis will be conducted at the end of the third year of the study to evaluate individuals who have had at least 1 year of follow-up. This analysis will verify whether the cessation of participant recruitment is warranted by the data collected thus far and will be an opportunity to revise sample calculations according to the results. Interim analysis will seek evidence of the effectiveness, or lack thereof, of chemoprophylaxis or any clear indications that the postulated effect is so unlikely that recruitment is no longer justified. The assessment will be based on the number of events accumulated thus far and the trend in the difference between comparison groups, and the discontinuation of the trial will be submitted to the Data Monitoring Committee.

The critical level of a *z* score to reject the null hypothesis in the interim analysis will be adjusted to 2.782 (*p* = 0.005) in line with the O’Brien-Fleming protocol [22]. The conservative criterion in the interim analysis protects the study from the often-misleading results obtained from smaller samples.

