### Intervention

All contacts included in the study receive a single supervised dose of rifampicin or placebo. Either rifampicin or placebo is administered during the initial visit, but only after each contact has signed the ICF, undergone anamnesis, been clinically examined, and had their data collected.

The rifampicin dose consists of 600 mg, or 10 mg/kg body weight in contacts weighing less than 40 kg. Infants and children receive the dosage in a solution determined by weight [15]. All contacts must receive the BCG vaccine a maximum of 2 months after the single dose of rifampicin or placebo.

Maintaining the blinding poses some challenges because rifampicin often leads to reddish-colored urine, tears, and sweat. Rifampicin and placebo capsules have identical organoleptic properties even though starch placebos do not mimic the reddish coloration in the urine and elsewhere.

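### The per-protocol rule deletes contacts for missed later steps with no exception for those who become cases first, and its 'and' leaves the excluded group unclear

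*Protocol article*

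**What the plan says.** All references are to the Methods of the protocol article.

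- **ITT (Statistical analysis):** "The total number of randomized participants will be analyzed to preserve the safeguards against selection bias and confounding".
- **Per-protocol (Statistical analysis):** presented as an alternative to ITT. It is to "disregard the data obtained from participants that did not meet the eligibility criteria and did not adhere to either of the intervention regimens" or to study procedures. The two conditions are joined by 'and'.
- **Stated reason:** the next sentence begins "Evaluating the group that adhered to the protocol prevents classification bias". Differences between the two analyses are to be read through the baseline characteristics of the adherent participants. The section concedes that protocol violations could undo the balance achieved by randomisation.
- **Steps after randomisation:** the Intervention section says "All contacts must receive the BCG vaccine a maximum of 2 months after the single dose of rifampicin or placebo". The Follow-up section adds visits at 2 and 12 months, blood sampling, and earlobe lymph sampling for those over 12. It withholds BCG from contacts under 1 year who were vaccinated before.
- **Outcome and time at risk:** the primary outcome is new leprosy during follow-up. The Cox analysis measures time from exposure "for each participant until disease develops or follow-up is discontinued".
- **Cases diagnosed elsewhere:** the Follow-up section plans a search of the national leprosy database (SINAN) to limit losses.

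**The concern.** A case that arises between the dose and the BCG visit is a primary-outcome event, because time starts at the dose. The per-protocol rule asks whether the contact completed steps that fall due later, and it discards all data of those who did not. If a contact becomes a case first and a later step is then missed, the exclusion is caused by the outcome. A contact diagnosed in another unit who misses the 12-month visit raises the same problem by another route: the SINAN search finds the case and the per-protocol rule can discard it.

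What is at stake is the per-protocol estimate and how a gap between it and ITT is explained. Loss of events because of the outcome need not show up as imbalance in baseline covariates, so the planned reading could point to the wrong cause. The section credits the per-protocol analysis with preventing one bias and does not mention that it can bring in this one.

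The 'and' is a separate drafting fault. Two analysts could build different per-protocol sets from the same sentence.

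**Working it through.** **1. Which contacts does the rule remove?**

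- *Literal reading:* ineligible and non-adherent together. An eligible non-adherent contact stays in. The set is then not the adherent group that the next sentence describes.
- *Intended reading:* ineligible or non-adherent. This matches the next sentence, and the outcome-related exclusion arises under it.

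The two readings cannot both hold. The second is the likelier intent.

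**2. Can a primary event be removed on the intended reading?** Time at risk starts at the dose. BCG falls due up to 2 months later and the final fixed visit at 12 months. The rule has no clause for a diagnosis that precedes a step. The only stated BCG exception is for vaccinated contacts under 1 year. Removal is therefore possible. The text does not say that it will happen.

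**3. Plan figures (Calculation of sample size).** Risks are 5% placebo and 2% rifampicin, so the implied ratio is 0.02/0.05 = 0.40. With the loss-inflated arms:

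- placebo 498 × 0.05 = 24.9, about 25 cases
- rifampicin 995 × 0.02 = 19.9, about 20 cases
- ratio (20/995)/(25/498) = 0.400

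The article gives no share of cases before BCG, so every split below is an assumption.

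**4. Deleting early cases from numerator and denominator.**

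Constant hazard over 12 months, equal early and overall effect: 25 × 2/12 = 4.2 and 20 × 2/12 = 3.3, rounded to 4 and 3.

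| Removed (placebo / rifampicin) | Per-protocol ratio |
|---|---|
| 4 / 3 | (17/992)/(21/494) = 0.403 |
| 6 / 2 | (18/993)/(19/492) = 0.469 |
| 8 / 2 | (18/993)/(17/490) = 0.522 |

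The first row deletes 7 of 45 events and leaves the ratio where it was. The other two assume that early cases concentrate in placebo.

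**5. Direction, in proportions.** Let f be the share of placebo cases that arise before BCG and h the rifampicin/placebo risk ratio for those early cases. After deletion:

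- placebo risk = 0.05(1 − f)/(1 − 0.05f)
- rifampicin risk = (0.02 − 0.05fh)/(1 − 0.05fh)

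| h | f = 0.10 | f = 0.30 |
|---|---|---|
| 0.2 | 0.0190/0.0452 = 0.42 | 0.0171/0.0355 = 0.48 |
| 0.4 | 0.0180/0.0452 = 0.40 | 0.0141/0.0355 = 0.40 |
| 1.0 | 0.0151/0.0452 = 0.33 | 0.0051/0.0355 = 0.14 |

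In the arms before loss inflation (415 and 829), f = 0.10 to 0.30 means about 2 to 6 placebo cases: 415 × 0.05 × f = 2.1 to 6.2.

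The ratio moves toward 1 if rifampicin works better early than overall, stays put if the effects are equal, and moves away from 1 if rifampicin works less well early.

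**6. The SINAN route.** The article does not say how many cases will be diagnosed elsewhere, so this cannot be sized. The planned loss allowance is 1493 − 1244 = 249 contacts, so missed visits are expected to be common.

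**The case against.** **No passage describes the removal.** The article does not say that a contact diagnosed before month 2 goes without BCG, or that missing BCG after a diagnosis counts as non-adherence. The flowchart is not available. Observing each participant until disease develops could be taken to mean that a case is complete at the event. This stands, and it is why the point is that such contacts can be removed, not that they are. 'Study procedures' is also not listed, so exclusion for a refused earlobe sample is a possible reading only.

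**A reader might infer that the rule removes the cases the trial most wants to prevent, mostly from placebo, and so pulls the per-protocol estimate toward no effect.** The documents do not support that. The Discussion part of the Abstract places the target cases in the months after vaccination, and those contacts have had BCG. The Follow-up section relies on slow progression over these 2 months, which suggests few early cases. The ratios 0.47 and 0.52 need assumed splits, and the direction depends on an early effect that nobody has stated.

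**ITT is untouched.** It keeps every randomised contact, and the per-protocol analysis is only the alternative. The article also does not say that baseline characteristics are the only thing to be examined, and deleted cases would show if event counts were compared. This stands and limits the weight of the point.

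**Per-protocol detail usually sits in the full protocol or SAP.** That would answer a complaint about missing detail. Here the article states the rule, the deletion of data and how discrepancies will be read, and its conjunction contradicts its next sentence.

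**Conclusion.** The point holds as a defect in the wording of a supporting analysis. On its likely meaning, the rule conditions on adherence after randomisation, deletes data instead of censoring, and gives no protection to cases that precede a step or are found only through SINAN. On its literal meaning, it does not produce the adherent group that the plan says it will analyse.

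No bias is demonstrated. It may be close to nil (0.400 to 0.403 under constant hazard and equal effects) or go either way (0.42 to 0.48 for an early ratio of 0.2; 0.33 to 0.14 for an early ratio of 1.0), with 10–30% of placebo cases arising before BCG. Both the early share and the early ratios are assumptions. The calculations also assume that every early case is deleted, which the documents do not state. The ITT result does not change. The correction is worth making because it is cheap and because, with about 45 expected events, a few deletions can be visible.

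**What to change.** Replace the per-protocol sentence with wording to this effect:

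> The per-protocol set consists of randomised contacts who met the eligibility criteria and received the allocated single dose; contacts who were ineligible or did not receive that dose are excluded. Time runs from the dose. Leprosy diagnosed before a study step falls due is an event and not non-adherence. A contact who later departs from the regimen is censored at the date of departure. Contacts under 1 year who were already vaccinated do not depart from the regimen by not receiving BCG. Missed laboratory procedures or visits do not exclude a contact from the primary-outcome analysis.

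Also:

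- Report, by arm, the cases that count in ITT but not in the per-protocol analysis, beside the planned comparison of baseline characteristics.
- Fix membership of the set before unblinding. The Randomization and blinding section says the 2:1 ratio makes a blinded analysis hard to maintain, so this should be settled before outcomes are set against allocation.

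The cost is wording only, since dose, BCG and diagnosis dates are already collected. There is a small downside. The set is less strictly one of completers, and censoring at a deviation assumes that the deviation carries no information about the risk of leprosy.

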### Randomization and blinding

The allocation of the participants into groups is based on random sequence generation via computer software (WINPEPI program, version 11.18). The ratio is 2:1 with two intervention groups and one control group for the purpose of expanding the pool of information generated by chemoprophylaxis. Participants will be randomly assigned to intervention or placebo in permuted blocks of variable sizes defined by the statistician, concealed from team members. Blocked randomization guards against any imbalance in the number of participants assigned to each group, a major concern for interim analysis, and also protects against the temporal variations in individual characteristics as well as in study procedures that may arise in long enrollment phases.

The intervention code (rifampicin/placebo) for each patient is placed in sealed opaque envelopes and numbered sequentially (natural numbers). The envelopes are only opened after each contact has voluntarily signed the ICF to avoid foreknowledge of the allocated group. The number printed outside the envelope identifies the participant and the opened envelopes are saved to ensure traceability. Self-adhesive tags identifying the code of each volunteer are pasted onto the recruitment form, ICF, blood collection tubes, and each patient identification card. Group assignment will be concealed from study participants and from the researchers, physicians, and research assistants performing the study procedures (double-blind) as a way of protecting it from any unconscious biases or expectations as to the outcome. Two nonblinded team members that do not participate in data collection and analyses are responsible for dispensing rifampicin and the placebo, opening and storing envelopes for randomization, labeling study documents, and administrating the medications. The allocation ratio (2:1) will make the intervention group twice the size of the control group, thus hampering the blinding of the statistical analysis of the data.

Besides preventing informational bias, blinding may additionally avert adherence problems in the placebo group. During follow-up, unblinding will be allowed whenever the clinical management of adverse events requires disclosure of the individual’s group to the attending physician and to the independent monitoring committee.

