### Analyses of outcomes based on immunological and molecular parameters

The quantitative variables analyzed will be those related to the ELISA results on anti-PGL1, LID-1, and IFN-γ. The optical density (OD) of each will be read at 450 nm. PGL-1 samples with OD > 0.25 will be considered positive while LID-1 samples will be considered positive with OD > 0.3. As for IFN-γ, the reading will be performed according to the manufacturer’s recommendations (eBioscience®, San Diego, CA, USA).

Frequency distribution will be constructed to detect asymmetries and the need for scale transformation. The primary analysis will address measures of the central tendencies (mean and median), and those of dispersion (i.e., interquartile range, variance, and standard deviation).

For the continuous variables, paired measurements for each individual will result from blood samples obtained before receiving rifampicin and during the contact visit 2 months after receiving rifampicin and before receiving the BCG vaccine. The results obtained 12 months after the first blood collection will also be submitted to paired analysis with the *t* test comparing the mean values of any changes between the two groups.

The main explanatory variable is intervention (rifampicin/placebo). Bivariate and multivariate analyses (linear regression model) will consider the following major covariates: age group, bacilloscopic index (BI), and type of coexistence with the index case. The response variables will include the anti-LID-1, anti-PGL-1, and IFN-γ measurements on a continuous scale. The effect of the intervention will be evaluated and adjusted for the effects of the other explanatory variables.

Regarding the PCR results (positive/negative), bivariate and multiple analyses (logistic regression model) will include the same previously mentioned explanatory variables: age group, BI, and type of cohabitation with the index case. A 5% significance level will be adopted, and 95% confidence intervals will be constructed for the estimates. Data management will use Microsoft Access®, and statistical analyses will be conducted using SPSS version 22.0 (IBM Corp., 2013).

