### Calculation of sample size

The sample size of this study was calculated on the basis of the primary outcome of the leprosy chemoprophylaxis among contacts using rifampicin associated with BCG vaccine. For the occurrence of this outcome a minimum follow-up time was set at 1 year.

Sample size calculations were based on the proportion of contacts that would likely develop leprosy per intervention group, currently estimated at 5% for the placebo group and 2% for the rifampicin group. With an allocation ratio of 2:1, the difference of 3 percentage points, a statistical power of 80%, and a significance level of 5%, (corrected to 0.025 to account for the interim analysis), the study requires 829 participants in the intervention group and 415 controls for a total 1244 participants. Estimating a 20% loss during follow-up (based on previous ASA data), the total sample size would total 1493 participants (995 in the treatment group and 498 controls). This sample size is appropriate for the analysis of time to failure enabling the study to detect more subtle effects (hazard ratio 0.67). Assuming a 30% seropositivity for PGL-1 among controls, this sample size will provide 85% power to detect an 8 percentage point difference from the treatment group. For 2.5% LID-positive controls, the study has 77% power to detect a 2 percentage point difference. For 35% IFN-γ-based susceptibility the study has an 80% power to detect an 8 percentage point difference. The calculations were performed via PASS11 software [23].

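### The adjusted Cox model for new leprosy cases takes its covariates from observed imbalance between the arms, so the adjusted hazard ratio is not fixed in advance; the log-rank test is unaffected

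*Protocol article*

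**What the plan says.** The Statistical analysis section gives one covariate rule for the primary outcome: the Cox analyses "will be conducted to adjust the association estimates (hazard ratio for new cases) for covariates with any imbalance in group distribution". It gives no prognostic criterion. The same section sets the role of the estimate: "The hazard ratio estimates the magnitude of the association between chemoprophylaxis and leprosy". Significance is handled separately: "The statistical significance will be assessed by the Log-Rank test". As described, that test uses no covariates.

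Age, BI and type of cohabitation appear for the primary outcome only as subgroup variables: subgroup analyses "according to age, along with the BI and type of cohabitation with the index case, will be carried out". For the laboratory outcomes the article does name covariates in advance. There, the bivariate and linear regression analyses "will consider the following major covariates: age group, bacilloscopic index (BI), and type of coexistence with the index case", and the logistic model for PCR uses the same set.

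The Randomization and blinding section describes allocation: "Participants will be randomly assigned to intervention or placebo in permuted blocks of variable sizes defined by the statistician". It names no stratification factors.

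**The concern.** In a properly randomised comparison of everyone allocated, a baseline difference between arms is chance. Whether a covariate helps the Cox model depends on how strongly it predicts leprosy. A rule triggered by imbalance looks at the wrong property. It can bring in variables unrelated to the outcome and drop a strong predictor because it happens to be balanced.

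The article itself points to such a predictor. Its Background section reports that early cases after vaccination arose mainly among contacts positive for anti-PGL-1, and the Follow-up section has the rapid anti-PGL-1 test done in all participants at the initial evaluation. Under the stated rule this marker enters only if the arms happen to differ on it.

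The model is also settled only once the arms have been compared, and it can change between the interim and final analyses as the pattern of imbalance changes. A shift in the adjusted hazard ratio could then reflect a different model and not new information. At stake are the fixity of the adjusted estimate and the precision that known risk factors could supply.

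**Working it through.** The covariate rule has no figure of its own to reproduce. The check uses the plan's arm sizes and event rates, and everything else is an assumption labelled as such.

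**1. Arm sizes and events.** The Calculation of sample size section gives 829 and 415 evaluable participants (995 and 498 with the loss allowance), 80% power, and event proportions "currently estimated at 5% for the placebo group and 2% for the rifampicin group". The pooled proportion is (0.05 + 2 × 0.02)/3 = 0.03. With two-sided 5% (the same as one-sided 2.5%):

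- Controls = [1.96 × √(0.03 × 0.97 × 1.5) + 0.8416 × √(0.05 × 0.95 + 0.02 × 0.98/2)]² / 0.03² ≈ 415.
- Total = 415 + 830 = 1245, against 1244 stated. The arm sizes reproduce.
- Expected events, evaluable: 415 × 0.05 + 829 × 0.02 = 20.75 + 16.58 = 37.3.
- Expected events, all enrolled and no loss: 498 × 0.05 + 995 × 0.02 = 24.9 + 19.9 = 44.8.

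**2. How often the rule fires by chance.** Assume that imbalance means p < a on each of k independent covariates. The chance that at least one is selected is 1 − (1 − a)^k:

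- k = 3: 14% at a = 0.05, 27% at a = 0.10.
- k = 5: 23% and 41%.
- k = 8: 34% and 57%.
- k = 10: 40% and 65%.

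The thresholds and counts are assumptions; the article states neither. With three prognostic covariates and a = 0.05, the chance that none is selected is 0.95³ = 86%.

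**3. What it does to the estimate.** The simulation used 829 versus 415 participants, one year of follow-up and 1,500 trials per scenario. It assumed eight independent baseline covariates, three of them prognostic (log hazard ratio 0.7, 0.7 and 0.5 per SD).

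True hazard ratio 0.4 (about 39 events):

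- No adjustment: geometric mean 0.411, rejection 78.4%.
- Adjustment for covariates imbalanced at p < 0.05: 0.411, rejection 78.2%.
- Prespecified adjustment for the three prognostic covariates: 0.396, rejection 80.3%.
- Largest against smallest hazard ratio within one trial, over no adjustment and thresholds of 0.05, 0.10 and 0.20: a factor of 1.03 (median) and 1.15 (95th percentile).

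Each rejection rate has a simulation standard error of about √(0.8 × 0.2/1500) = 1.0 point, so the gap of 2 points is approximate.

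True hazard ratio 1 (about 64 events):

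- Two-sided rejection was 4.3% unadjusted, 4.0% prespecified and 3.8% with imbalance selection.
- Taking the most favourable of the four models moved the geometric mean from 1.027 to 1.005 and left rejection in rifampicin's favour at 2.0%.

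**4. Room for covariates.** Treatment plus three single-parameter covariates is 4 parameters: 37.3/4 = 9.3 to 44.8/4 = 11.2 events each. With a fourth covariate it is 37.3/5 = 7.5 to 44.8/5 = 9.0.

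**The case against.** The strongest reply is about scope. Significance rests on the log-rank test, bivariate analyses of intervention against outcome are also planned, and nothing says that the adjusted hazard ratio is the headline result. This stands. A reader might infer that the primary test is compromised or that false positives rise. The article does not support the first, since the test as described has no covariates, and the simulation shows no sign of the second.

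Second, not every imbalance is chance. Just before the rule, the article notes that protocol violations could upset the balance achieved by randomisation. In the per-protocol set, adjusting for imbalance has a rationale. This stands and limits the point to the intention-to-treat set. It does not remove it, because the rule is not confined to the per-protocol analysis.

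Third, the Randomization and blinding section concedes that the 2:1 ratio hampers blinding of the analysis, and a reader might infer that the model will be chosen to favour rifampicin. The rule as stated uses baseline data and not outcomes, and even the most favourable of the four simulated models left rejection in rifampicin's favour at 2.0%.

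Fourth, a condensed article may leave the candidate list and the definition of imbalance to an analysis plan. This is granted, and their absence is not held against it. The selection criterion itself is stated, however, and a list or threshold added elsewhere would still be triggered by observed imbalance.

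The laboratory section is no second instance of the problem. It fixes covariates in advance, and serves here as a contrast.

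**Conclusion.** The point holds for the adjusted intention-to-treat hazard ratio. The stated rule selects covariates by a property that, under randomisation, carries no information about prognosis. The result is an estimate not fixed in advance and precision left to luck. In the simulation the rule performed almost exactly like no adjustment.

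The size is modest: about 2 points of power against prespecified adjustment, and hazard ratio shifts of usually a few percent, up to about 15%. These figures depend on the assumed number of covariates, their independence, their prognostic strength and the imbalance thresholds. The chance of 14% (three covariates) to 40% (ten) that at least one is selected assumes a 5% test that the article does not mention. It measures how often the rule fires and is not a measure of bias.

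A reader might also infer overfitting or invalid standard errors. Neither is shown: the number of covariates that would enter is unknown, and rejection under the null was not above 5%. The event count of 37 to 45 applies the plan's 5% and 2%, which were set for a minimum of one year. Case ascertainment to July 2021 could raise it.

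**What to change.** In the Statistical analysis section, replace the imbalance criterion with a named list for the intention-to-treat Cox model: age group, BI of the index case and type of cohabitation. These are the covariates already named for the laboratory and PCR models. Enter them regardless of observed balance, and use the same set at the interim and final analyses.

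Keep the categories few, ideally one parameter per covariate, given the expected 37 to 45 events. The baseline rapid anti-PGL-1 result may replace one of the three if the parameter count allows; adding it as a fourth covariate takes the model below 10 events per parameter.

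Keep the log-rank test for significance, as now planned. Retain imbalance-driven adjustment only as a labelled sensitivity analysis or for the per-protocol set.

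The cost is a change of wording. The variables are already planned for collection or use, and the sample size does not change.
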